### Strategies to improve adherence to interventions {11c}

The principal researcher will offer 2–3 individual online consultations via Line App to answer questions about the decision-aid and clarify information within the decision-aid. Women will be directed back to their provider for questions specific to their pregnancy and decision making.

### Relevant concomitant care permitted or prohibited during the trial {11d}

Since there is no invasive intervention involved in this study, there will be no physiological risks involved in this study. Thus, no concomitant care and interventions are prohibited. The only psychological risk is the emotional distress that may arise from the sensitive questions asked during the counseling process. This study will provide personal assistance or referral to the relevant counseling department or support groups.

### Provisions for post-trial care {30}

There is no anticipated harm and compensation for trial participation.

### Outcomes {12}

Primary outcome measures include decisional conflict (time frame: 14–16-weeks’ gestation and 35–38 weeks’ gestation), knowledge (time frame: 14–16-weeks’ gestation and 35–38 weeks’ gestation), birth mode preference (time frame: 14–16-weeks’ gestation and 35–38 weeks’ gestation), and decision-aid acceptability (time frame: 35–38-weeks’ gestation).Secondary outcome measures include actual birth outcome (time frame: one month after birth) and satisfaction with decision scale (SWD) (time frame: one month after birth).

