### Sample size {14}

Sample size was calculated using G-POWER 3.1.9.2 software. Based on estimates from a previous pilot study [39], effect size = 0.50, a total of sample size 128 provided α = 0.05 and power = 0.80. To allow for preterm deliveries, mal-presentations, and losses to follow-up, an increase in the desired number by 20 percent would be 154.

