## Assignment of interventions: allocation

### Sequence generation {16a}

Using computer permuted block randomization.

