## Statistical methods

### Statistical methods for primary and secondary outcomes {20a}

Analysis will be by intention to treat. Data will be processed and analyzed using IBM SPSS version 28.0 software. Descriptive statistical analysis will include frequency, percentage, mean and standard deviation for each variable; chi-square test and Student’s t-test will be used to compare the differences between groups for the homogeneity of basic attributes. Statistical significance will be established using an α of 0.05. Bivariate analyses and linear regression models will be used to examine determinants of primary outcomes (decisional conflict score, knowledge score, birth mode preference), and secondary outcomes (mode of birth and satisfaction with decision). The strength of women’s birth mode preference will be analyzed using a non-parametric test (Wilcoxon signed-rank test).

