### Methods for additional analyses (e.g. subgroup analyses) {20b}

Analysis of decision aid acceptability subgroup will be conducted to assess the differences between control and intervention group.

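### Four outcomes are called primary without ranking (the analysis section counts three), while the sample size fits one test at 0.05 and names no outcome, so 5% error and 80% power attach to no stated claim

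*Protocol article*

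**What the plan says.** **Outcomes {12}.** The sentence that begins "Primary outcome measures include decisional conflict" names four primary outcomes: decisional conflict, knowledge, birth mode preference and decision-aid acceptability. None is ranked above another.

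**Statistical methods {20a}.** One threshold is given: "Statistical significance will be established using an α of 0.05". The same section speaks of "determinants of primary outcomes (decisional conflict score, knowledge score, birth mode preference", which is three outcomes. Acceptability is not among them.

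**Additional analyses {20b}.** Acceptability appears here instead: "Analysis of decision aid acceptability subgroup will be conducted to assess the differences between control and intervention group". According to the intervention description and the acceptability measure, this scale rates the web platform, and only the intervention arm has access to that platform.

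**Sample size {14}.** One calculation is reported: "effect size = 0.50, a total of sample size 128 provided α = 0.05 and power = 0.80". The effect size is attributed to a pilot study, but the outcome it describes is not named. The total is raised by 20% to 154.

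**The concern.** A sample size built on one test at the full 0.05 implies one deciding outcome. The outcome section supplies four of equal standing, and the statistical section three. The document does not say whether the aid counts as effective when one primary outcome succeeds, when all do, or when a first-ranked one does.

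The trial's main claim depends on that choice. Without a lead outcome, the decision aid could be called effective on whichever primary measure reached p<0.05, at an error rate well above 5%. Under a stricter rule, the 80% power in the sample size section would no longer describe the trial's chance of success.

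**Working it through.** **Inputs from the protocol.** Number of primary outcomes k = 4 (Outcomes {12}) or k = 3 (Statistical methods {20a}); α = 0.05; d = 0.50; power 0.80; N = 128.

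**Assumptions.** The sample size section names the software ("Sample size was calculated using G-POWER 3.1.9.2 software") but neither the test nor its sidedness, and the sequence section says only "Using computer permuted block randomization". I assume a two-sided two-sample t-test, 1:1 allocation, and one between-arm test per primary outcome. The document gives no correlations between outcomes, so a common value of 0.3, 0.5 or 0.8 is shown beside independence.

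**1. Reproduce the plan's figure.** With n per arm, the noncentrality is d√(n/2). At n = 64 this is 0.50 × √32 = 2.83 on 126 degrees of freedom. Two-sided power at 0.05 is 80.1%; at n = 63 it is 79.5%. So 64 per arm, or 128 in total, is reproduced exactly. The normal approximation gives 126; a one-sided normal calculation gives 100 and does not fit. The increase is 128 × 1.2 = 153.6, rounded to 154.

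**2. Any one primary outcome at 0.05 counts as success.** Under independence the family-wise error is 1 − (1 − 0.05)^k:
- k = 3: 1 − 0.95³ = 14.3%
- k = 4: 1 − 0.95⁴ = 18.5%

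With correlated normal test statistics:

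| Assumed correlation | 3 tests | 4 tests |
|---|---|---|
| 0 | 14.3% | 18.5% |
| 0.3 | 13.6% | 17.4% |
| 0.5 | 12.5% | 15.6% |
| 0.8 | 9.8% | 11.4% |

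**3. α is split by Bonferroni.** The same noncentral-t calculation at d = 0.50:

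| | 3 tests (0.05/3 = 0.0167) | 4 tests (0.05/4 = 0.0125) |
|---|---|---|
| Power per outcome, N = 128 | 65.6% | 61.6% |
| Power per outcome, all 154 analysed | 75.1% | 71.7% |
| N for 80% per outcome, before dropout | 172 | 182 |
| Chance of at least one success, N = 128, correlation 0 / 0.5 / 0.8 | 96% / 88% / 80% | 98% / 89% / 80% |

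The last row requires d = 0.50 on every outcome.

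**4. All primary outcomes must succeed at 0.05.** The chance of a false overall claim is at most 5%. Joint power, with d = 0.50 on every outcome:
- Independent: 0.801³ ≈ 51%; 0.801⁴ ≈ 41%
- Correlation 0.5: about 62% (three), 57% (four)
- Correlation 0.8: about 70% (three), 67% (four)

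The correlated power figures in steps 3 and 4, and the at-least-one figures, use a normal approximation that gives 80.7% for a single test, so they run slightly high.

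**5. One lead outcome, or a fixed order.** The first test uses the full 0.05. Error is 5% and power 80.1% at N = 128.

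**The case against.** **The silence may be filled elsewhere.** This is a condensed article, and a multiplicity method is often left to an analysis plan that is not shown here. That is fair: the absence of an adjustment is not the finding. What stands is that the stated labels, α and sample size do not match one another. A later α split would also not restore 80% power per outcome at 128 women.

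**The family may be three.** The statistical section lists three outcomes, and acceptability rates something the control arm does not receive. This stands, so both sets of figures are given. It is also an inconsistency in its own right, and the conclusion is the same for three or four.

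**A reader might infer that the trial has neither a 5% error rate nor 80% power.** The document does not support that. The two failures belong to different success rules. If all must succeed, the error rate is controlled and only power falls. If any one suffices under Bonferroni, the chance of at least one success remains near or above 80% when d = 0.50 holds throughout, and the loss is per outcome. A fixed order keeps both properties for its first test.

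**A reader might take 41% as the trial's power.** That needs four tests, an all-must-succeed rule and independence. The outcomes measured before birth are collected from the same women in one survey, so independence is unlikely.

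**A reader might assume the 0.50 refers to decisional conflict.** The sample size section does not say so.

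**Conclusion.** The concern holds in this form: the protocol names four unranked primary outcomes in one section and three in another, sets one α, and sizes the trial for a single test on an unnamed outcome. The sample size arithmetic itself is correct.

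The consequence depends on the unstated success rule. Reading any primary outcome at p<0.05 as success gives a family-wise error of about 10% to 14% for three tests or 11% to 19% for four, across correlations from 0.8 down to 0. Splitting α lowers power per outcome from 80.1% to 65.6% or 61.6%. Requiring every outcome to succeed keeps error at or below 5%, with joint power between about 51% and 70% (three) or 41% and 67% (four).

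These figures rest on two-sided between-arm t-tests, 1:1 allocation and assumed correlations. The statistical section assigns preference strength a signed-rank test, which is a paired method, so treating that outcome as a t-test between arms is an approximation.

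**What to change.** Before any comparison by arm:

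1. Designate one lead primary outcome and state that the 80% power applies to it at two-sided 0.05. Decisional conflict at 35–38 weeks is a natural candidate if the pilot's 0.50 refers to it; otherwise choose the outcome to which it does refer.
2. Make the remaining outcomes secondary and test them in fixed sequence or with Holm.
3. Report acceptability descriptively.
4. Bring Outcomes {12}, Statistical methods {20a} and Additional analyses {20b} into agreement on which outcomes are primary.

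**Cost.** Recruitment began in September 2021, so this changes the primary outcomes of a running trial. It needs a documented amendment, ethics review and a registry update, and the other outcomes lose equal primary status. No extra women are needed.

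**If the arms have already been compared,** choosing a lead outcome is no longer credible. Keep all the primary outcomes and report them together with a stated multiplicity adjustment and the reduced power per outcome.

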### Participant timeline {13}

Eligible women will be invited to participate in the study when they attend prenatal examination at the 14–16 weeks’ gestation visit in the Outpatient Department of Obstetrics and Gynecology within the hospital study site. After participants sign written consent for participation, they will be randomly allocated to either the control group or intervention group by the principal researcher. All participants will initially complete an online google survey including ‘personal demographic information’, ‘decision conflict scale’ ‘knowledge scale’ and ‘birth mode preference’. After completing the questionnaires, women allocated to the intervention group and the principal researcher will provide women a username and password to log into the birth decision-aid platform. The principal researcher will encourage women to discuss information with their families. They will be encouraged to use the decision-aid during recruitment and at each visit in the hospital Outpatient Department of Obstetrics. To answer questions and clarify information about the decision-aid, an online individual consultation with the principal researcher will be provided for women in the intervention group at least twice during the 17–34 weeks’ gestation. A first-time follow up survey will be held at 35–38 weeks’ gestation, including decision conflict scale, knowledge, birth mode preference, and decision-aid acceptability. All participants confirm preferred birth mode with their obstetrician prior to completing the first-time follow up. A second-time follow up is held one month after birth. Postnatal women will complete a “satisfaction” questionnaire when they attend their postnatal examination visit (Fig. 3).

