**Methods:**

A quantitative approach will be adopted using a randomized pre-test and post-test experimental design in a medical centre in northern Taiwan. The web-based decision aid consists of five sections. Section 1 provides a two-part video to introduce SDM and how to participate in SDM. Section 2 presents an overview of functions and features of the birth decision-aid. Section 3 presents relevant VBAC information, including definitions, benefits and risks, and an artificial intelligence (AI) calculator for rate and likelihood of VBAC success. Section 4 presents the information regarding elective repeat caesarean delivery (ERCD), involving definitions, benefits, and risks. Section 5 comprises four steps of decision making to meet women’s values and preferences. Pregnant women who have had one previous caesarean and are eligible for VBAC, will be recruited at 14–16 weeks. Participants will complete a baseline survey prior to random allocation to either the control group (usual care) or intervention group (usual care plus an AI-decision aid). A follow up survey at 35–38 weeks will measure change in decisional conflict, knowledge, birth mode preference, and decision-aid acceptability. Actual birth outcomes and satisfaction will be assessed one month after birth.

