## Assignment of interventions: Blinding

### Who will be blinded {17a}

Participants will be blinded to their allocation after assignment to interventions. Data entry and analysis will both be blinded.

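### The abstract places the baseline survey before randomisation and the participant timeline places it after, so it is unclear whether the pre-test of three primary outcomes precedes allocation.

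*Protocol article*

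**What the plan says.** The Methods paragraph of the abstract is explicit: "Participants will complete a baseline survey prior to random allocation to either the control group (usual care) or intervention group".

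Participant timeline {13} sets out the first visit in four consecutive steps. Consent comes first and leads directly to allocation, and the survey is described next. Once they have signed, women are "randomly allocated to either the control group or intervention group by the principal researcher. All participants will initially complete an online google survey", which covers demographics, decisional conflict, knowledge and birth mode preference. The login follows: "After completing the questionnaires, women allocated to the intervention group and the principal researcher will provide women a username and password".

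The baseline measurement belongs to the primary outcomes. Outcomes {12} states: "Primary outcome measures include decisional conflict (time frame: 14–16-weeks’ gestation and 35–38 weeks’ gestation", and gives the same two time points for knowledge and birth mode preference.

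On who knows what, section {17a} states: "Participants will be blinded to their allocation after assignment to interventions". It also says that data entry and analysis are blinded, but does not mention data collection. Under {16c} the principal researcher generates the sequence, enrols and assigns. Under {18a} the same person, with an assistant, collects the data.

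**The concern.** Trial design {8} describes a pre-test and post-test experiment, and the abstract says the follow-up survey measures change. The baseline score is therefore half of the measurement for decisional conflict, knowledge and preference. A score recorded before allocation cannot be affected by the arm. A score recorded after allocation has that protection only if neither the woman nor anyone dealing with her lets the arm influence it.

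Two things are at stake if the timeline order is used:

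- **Answers.** All three measures are self-reported. Decisional conflict and preference are attitudes, and could move if a woman learns which arm she is in or senses it from the researcher.
- **Loss.** A woman who withdraws between allocation and survey leaves no baseline. Section {20c} plans a complete-case analysis, so any analysis using baseline would omit her, and such losses could differ between arms.

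**Working it through.** **Check of the planned effect used as a yardstick.** Sample size {14} gives an effect size of 0.50, α = 0.05, power 0.80 and a total of 128. A two-sided, two-sample t-test with these inputs needs 63.77 per arm, rounded up to 64, so 2 × 64 = 128, with power 0.801. The figure reproduces. This point does not dispute it, and the order of baseline and allocation does not change it.

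**The two orders side by side.**

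| Step | Abstract, Methods | Participant timeline {13}, in text order |
|---|---|---|
| 1 | Baseline survey | Consent |
| 2 | Random allocation | Random allocation |
| 3 | – | Baseline survey |
| 4 | – | Login for the intervention arm |

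The abstract does not mention consent or login at this point. What differs is the relative position of survey and allocation. In the timeline, allocation is tied to consent and login is tied to completion of the questionnaires. The survey sentence is tied to neither, apart from the word *initially*. Taken in sequence, allocation comes first.

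**Who could know the arm at baseline, on the timeline order.**

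- The principal researcher knows it, having generated the sequence and made the assignment.
- The woman might know it. The text does not say she is told before the survey, and the login that would reveal it comes afterwards.
- No woman has used the decision aid by then. Login follows the survey, and the consultations run from 17 to 34 weeks. The risk is awareness of the arm, not exposure to the intervention.

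**How a shift would carry through (illustration only).** Let Δ be the true between-arm difference at 35–38 weeks, s the shift in the intervention-arm baseline caused by knowing the arm, and b the regression slope on baseline. All are in SD units, with no shift in the control arm.

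- Change score: estimate = Δ − s, so the bias has size s.
- Baseline-adjusted regression: estimate = Δ − b·s, so the bias has size b·s.
- Follow-up scores alone: estimate = Δ, with no bias by this route.

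Neither s nor b is in the documents. Assuming b = 0.5 and dividing by the planned 0.50:

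| Assumed s | Change score: bias (share of 0.50) | Adjusted, b = 0.5: bias (share of 0.50) |
|---|---|---|
| 0.1 | 0.10 (20%) | 0.05 (10%) |
| 0.2 | 0.20 (40%) | 0.10 (20%) |
| 0.3 | 0.30 (60%) | 0.15 (30%) |

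If s = 0, all biases are zero. A shift in the same direction as the true effect makes it look smaller; a shift in the opposite direction makes it look larger.

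**The case against.** The strongest reply is that this is a loosely written paragraph and not a faulty design. *Initially* may mean that the survey is the first study procedure, with the preceding sentence merely announcing that women are randomised. The abstract is unambiguous, and nothing gives the timeline precedence over it. The SPIRIT schedule (Fig. 3) and the study protocol diagram (Fig. 4) may settle the order, and neither is visible here. This stands as a limit: the documents do not show which order was used in practice. It does not remove the conflict, because one loose word cannot reconcile two differing sequences.

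A second reply is that participants are said to be blinded and that login follows the survey, so nothing in the text reveals the arm to a woman at baseline. This also stands in part, and is why her knowledge is only a possibility. It does not cover the principal researcher. The survey is completed online, which limits that person's influence without excluding it.

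A reader might go further and infer that any baseline taken after allocation biases the treatment effect, by 40% of the planned effect for a change score or 20% with adjustment. The documents do not support that. Timing alone causes no bias; answers or drop-out must also respond to knowledge of the arm. The percentages come from an assumed shift and slope. Section {20a} names bivariate analyses, linear regression and a Wilcoxon signed-rank test, without specifying a change score or baseline adjustment for the between-arm comparison. One common shift for three different outcomes is also doubtful: a true/false/unsure knowledge test is less likely to move than an attitude scale.

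**Conclusion.** The point holds as an internal contradiction with a real but unquantified risk. The abstract and Participant timeline {13} give different orders for baseline and randomisation, and a reader cannot tell which applies. If the timeline order is followed, the pre-test of three primary outcomes is taken after allocation, with the arm known to the person who assigns it and helps collect the data, and possibly to the women. Any resulting bias depends on how far that knowledge changes answers or retention, and on whether the analysis uses baseline. Its size and direction are unknown. If practice followed the abstract, the only defect is in the wording of the timeline.

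**What to change.** 1. Rewrite Participant timeline {13} to match the abstract: consent, baseline survey submitted, allocation released, login issued to the intervention arm. Check that Figs. 3 and 4 show the same order.
2. Make a submitted baseline survey a condition for releasing the allocation.
3. Recruitment began on September 15, 2021 (Trial status), so for women already enrolled compare survey and allocation times where both are recorded. Flag any baseline completed after allocation, and report how many women cannot be classified.
4. If any are flagged, add a sensitivity analysis that does not use those baselines, for example a between-arm comparison of the 35–38-week scores alone. This keeps the women in the intention-to-treat comparison.

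The cost is small: two steps reordered at the same visit, a corrected paragraph, and a retrospective check of times. The sample size is unaffected.

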**Fig. 3 Fig3:**
[figure not shown]
SPIRIT time schedule of enrolment, interventions, and assessments

### Sample size {14}

Sample size was calculated using G-POWER 3.1.9.2 software. Based on estimates from a previous pilot study [39], effect size = 0.50, a total of sample size 128 provided α = 0.05 and power = 0.80. To allow for preterm deliveries, mal-presentations, and losses to follow-up, an increase in the desired number by 20 percent would be 154.

### Recruitment {15}

Participants will be recruited from the Outpatient Department of Obstetrics and Gynaecology.

## Assignment of interventions: allocation

### Sequence generation {16a}

Using computer permuted block randomization.

### Concealment mechanism {16b}

A parallel group of participants will be allocated to either control group (usual care) or intervention group (usual care plus the birth decision-aid platform) in a quiet examination room in accordance with sequentially numbered computer permuted block randomization.

